#### fMRI data analysis

##### Neuroimaging data preprocessing

The DICOM software (version 1.3.5) will be used to convert the BOLD fMRI data into an analyzable NIFTI file. Preprocessing will be based on the MATLAB 2013b software platform with DPARSF V1.0 and SPM12 software. The preprocessing steps include removing the first 10 time points, time-layer correction, head-motion correction, spatial standardization, smoothing, delinear trends, noise filtering, and regression covariates.

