### Sample size

Due to the particularity of the neuroimaging mechanism, the clinical sample calculation method is not applicable. According to fMRI sample size research, each group should include at least 6–12 patients (40), while the statistical data of 20 subjects resembles that of large sample data for 130 subjects (41). Considering the uncertain factors in this study, including the loss or elimination of subjects and unavailable data due to head movements, we included 50 patients and 25 matched healthy persons in this study.

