##### Resting-state functional connectivity analysis

Based on the MATLAB 2013 software platform, the SPM12 software package will be used to perform the statistical analysis of brain functional connectivity. The whole-brain functional connectivity algorithm will be used to calculate the average time-series of all voxels at seed points. Next, all average time-series will be calculated individually with the Pearson correlation coefficient or the whole-brain voxel time-series. The correlation coefficient between the voxel and seed point can be obtained for each whole-brain voxel and transformed into an approximate Gaussian distribution data value using the Fisher-Z transform. Brain regions with significant statistical relationships will be identified according to a specific threshold and will be considered to have a resting-state functional connection with the seed points.

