##### Dynamic functional connection analysis

The Dynamic BC 2.4 toolkit will be employed to analyze the dynamic functional connectivity network, and the sliding window correlation (SWC) method to analyze the dFC characteristics. Based on previous experience, a window length of 30TR (60 s) and a sliding step size of 1TR will be applied to generate 200-time windows. For each window, the intravoxel time-series Pearson correlation of the ROI will be individually calculated. Subsequently, each subject will produce a sequence of sliding window correlation coefficients, which will be transformed to a normal distribution using Fisher’s z-conform. The variation in the correlation coefficient time-series will be represented by calculating the standard deviation of the *z*-value for each voxel to characterize the dFC variability. Time means, standard deviations, and coefficients of variation will be used to analyze the specific attributes of dFC.

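### Noise filtering is listed before covariate regression and no matching filter is applied to the covariates, so with raw motion regressors and a usual band-pass much motion-induced seed correlation can remain

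*Protocol article*

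**What the plan says.** The protocol article, under Neuroimaging data preprocessing, opens its list with "The preprocessing steps include removing the first 10 time points, time-layer correction" and closes it with "head-motion correction, spatial standardization, smoothing, delinear trends, noise filtering, and regression covariates". The software is named (DPARSF V1.0 and SPM12). The covariates and the pass band are not named, and nothing says whether the covariates are filtered.

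The later imaging sections take the preprocessed series as given. Resting-state functional connectivity analysis will "calculate the average time-series of all voxels at seed points" and correlate them with other voxels. Dynamic functional connection analysis uses "a window length of 30TR (60 s) and a sliding step size of 1TR", giving 200 windows. Neither section returns to the order of preprocessing. The Sample size section expects some "unavailable data due to head movements".

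**The concern.** Realignment parameters are estimated at the head-motion correction step. Filtering the images later does not filter those parameters. If they enter the final regression as they stand, the left side of the model is band-limited and the right side is broadband. Two things follow. The coefficients are fitted partly against frequencies where the data have been emptied, so they are too small and in-band motion stays in the residuals. The out-of-band part of the regressors is also subtracted from data that no longer contain it, which puts back noise the filter had removed. Tissue signals taken from already filtered images would not raise this problem; the motion parameters would.

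Motion shared by two voxels raises their correlation. Static connectivity, dynamic connectivity, microstates and the correlations with clinical and microbiota data all start from these residuals. If movement differed between patients and controls, or between arms at week 4, leftover motion could be read as a disease feature or a treatment effect. The article does not document such a difference.

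**Working it through.** The plan gives no figure for residual motion, so there is none to reproduce. The check asks what the listed order does if followed.

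**Inputs from the article.** TR is 2 s, so the Nyquist frequency is 1/(2 × 2) = 0.25 Hz. With 200 windows of 30 TR at step 1, the series has (200 − 1) × 1 + 30 = 229 volumes, or 239 before the first 10 are dropped.

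**Assumptions, not in the article.** Pass band 0.01–0.08 Hz, 0.01–0.10 Hz, or high-pass only at 0.01 Hz. Six raw motion regressors, or 24 (the six, their lags, and the squares of both). Seven motion spectra. True correlation between the two signals is 0.

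**Algebra, one regressor.** Let x be the motion regressor with variance σ², F an ideal filter, f the share of x's power inside the band, and β the true motion coefficient.
- Regressing Fy on unfiltered x gives slope βf instead of β.
- Residual motion is β(Fx − f·x), with variance β²σ²f(1 − f).
- Filtered motion before regression has variance β²σ²f, so the fraction left is 1 − f.
- Of the residual motion variance, the out-of-band part is β²σ²f²(1 − f), a share f.

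**Numbers for white motion, 0.01–0.08 Hz.** f = 0.07/0.25 = 0.28, so 72% of the motion variance is left. With in-band motion variance equal to signal variance:
- correlation without regression: 1/(1 + 1) = 0.50;
- after filtering, then regression: 0.72/1.72 = 0.42 (simulated: 0.41);
- out-of-band share of residual variance: 0.28 × 0.72/1.72 = 0.20/1.72 ≈ 12%.

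With a quarter of that motion variance, the correlation goes from 0.25/1.25 = 0.20 to 0.18/1.18 = 0.15. The proportion left is similar, but the absolute bias is smaller in people who move less.

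**Simulation.** 300 runs per case, with motion scaled so that the correlation without regression is about 0.50. Share of that correlation left after filtering and then regressing on raw regressors (six / 24):

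| Motion | 0.01–0.08 Hz | 0.01–0.10 Hz | High-pass only |
|---|---|---|---|
| White | 84% / 69% | 78% / 61% | 7% / 7% |
| Autoregressive, 0.5 | 63% / 53% | 56% / 47% | 16% / 15% |
| Autoregressive, 0.9 | 60% / 56% | 57% / 53% | 51% / 45% |
| Random walk | 71% / 62% | 71% / 62% | 68% / 55% |
| Spikes | 84% / 70% | 78% / 62% | 6% / 5% |
| Respiratory-type | 96% / 85% | 95% / 82% | 1% / 1% |
| Wholly in band | 0% / 1% | 2% / 2% | 2% / 2% |

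With six regressors, regressing before filtering, or giving the regressors the same filter, left a mean correlation between −0.01 and 0.01 in every case.

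A separate simulation (1,000 runs per scenario, six parameters, the two band-passes, five motion types) agrees. With artefact SD 0.5 times signal SD, mean spurious Fisher z was 0.15–0.20 without regression and 0.09–0.15 after the listed order. With SD equal to signal SD it was 0.41–0.56 and 0.26–0.46. About 60–80% survived, and 4–15% of residual variance was out-of-band noise put back.

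Both simulations cover correlation over a whole run. No sliding-window or microstate measure and no between-group bias was computed.

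**The case against.** The strongest reply is that the flaw needs premises the article does not state. The list is introduced by a verb that does not promise an order. The covariates, the pass band and any filtering of the regressors are unstated, and a condensed article may leave such detail to a fuller imaging protocol. With identically filtered regressors the listed order is harmless, and what the software does with covariates cannot be settled from this text. This stands as a limit on size and certainty. It does not remove the point: the list runs from volume removal through slice timing, realignment, normalisation, smoothing and detrending, which is plainly a processing order, and its last two items are in the unfavourable order. That is a poor stated sequence, not merely a missing detail.

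A reader might go further and infer that most motion-induced connectivity stays in every static and dynamic value. The documents do not support that. The share left runs from about 0% to 96% depending on unstated choices, people who move little are little affected, and dynamic connectivity was not simulated.

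A reader might also infer a false disease or acupuncture effect. That is conjecture: no group difference in movement is documented, and randomisation balances baseline movement between the arms in expectation. Realignment, and the loss of motion-affected scans that the Sample size section allows for, should reduce the artefact too.

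**Conclusion.** The point holds in conditional form. As listed, filtering precedes covariate regression and no step filters the covariates to match. Given raw motion parameters among the covariates and a band-pass of 0.01–0.08 or 0.01–0.10 Hz, roughly half or more of the motion-induced seed correlation can remain when motion is broadband, spiky or drifting. If motion is wholly in band almost none remains; with high-pass filtering only, the range is 1–68%. The size for dynamic connectivity, microstates and group contrasts is unknown. UAS7, the declared primary outcome, is unaffected. The imaging measures are the article's main mechanistic evidence and the remedy is nearly free, so the text should be corrected; confidence is medium because the decisive settings are not stated.

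**What to change.** In Neuroimaging data preprocessing, do one of three things: place covariate regression before noise filtering; carry out both in one joint step; or keep the order and state that the identical filter is applied to every covariate. The same sentence should name the covariates and the pass band, so that the choice can be checked.

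The cost is a batch setting and a sentence, plus a few degrees of freedom per scan if filtering and regression are done jointly. No patients or new scans are needed. If the pipeline in use already does one of these, only the sentence needs to change.

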##### Region of interest

Our previous studies found that multiple “DMN” core brain regions are closely related to urticaria, dyssomnia, and mood disorders. Their MNI coordinates are as follows: orbitofrontal cortex (*X* = −45, *Y* = 24, *Z* = −12), superior frontal cortex (*X* = −15, *Y* = 33, *Z* = 54), precentral gyrus (*X* = 48, *Y* = 9, *Z* = 33), angular gyrus (*X* = 45, *Y* = −48, *Z* = 33), and hippocampal gyrus (*X* = −18, *Y* = −12, *Z* = −9). These five brain regions were selected as regions of interest (ROI) to complete the resting-state, dynamic functional connectivity, and microstate analyzes.

##### Resting-state functional connectivity analysis

Based on the MATLAB 2013 software platform, the SPM12 software package will be used to perform the statistical analysis of brain functional connectivity. The whole-brain functional connectivity algorithm will be used to calculate the average time-series of all voxels at seed points. Next, all average time-series will be calculated individually with the Pearson correlation coefficient or the whole-brain voxel time-series. The correlation coefficient between the voxel and seed point can be obtained for each whole-brain voxel and transformed into an approximate Gaussian distribution data value using the Fisher-Z transform. Brain regions with significant statistical relationships will be identified according to a specific threshold and will be considered to have a resting-state functional connection with the seed points.

##### Dynamic functional connection analysis

The Dynamic BC 2.4 toolkit will be employed to analyze the dynamic functional connectivity network, and the sliding window correlation (SWC) method to analyze the dFC characteristics. Based on previous experience, a window length of 30TR (60 s) and a sliding step size of 1TR will be applied to generate 200-time windows. For each window, the intravoxel time-series Pearson correlation of the ROI will be individually calculated. Subsequently, each subject will produce a sequence of sliding window correlation coefficients, which will be transformed to a normal distribution using Fisher’s z-conform. The variation in the correlation coefficient time-series will be represented by calculating the standard deviation of the *z*-value for each voxel to characterize the dFC variability. Time means, standard deviations, and coefficients of variation will be used to analyze the specific attributes of dFC.

##### Brain micro-states extraction technology

Based on the dynamic functional connectivity network extraction, the k-means clustering method will be used in the dynamic functional connectivity matrix by cluster analysis to obtain the microstates of dynamic functional connectivity. Next, we will study brain functional connectivity changes in these microstates. The K-means algorithm uses a simple iterative strategy to divide the dataset into K nonoverlapping clusters. First, we will obtain the whole-brain dynamic functional connection vectors of all participants via vectorization in the upper triangular matrix of the dynamic functional connection matrix. Then, all functional connection vectors with strong variability (>1 SD) will be selected as clustering samples. The average diameter of each clustering result will be calculated to obtain the optimal number of clusters. The results will then be transformed into matrix form by running the standard k-means algorithm with the optimal clustering number on each subject’s dynamic functional connection vector. After summarizing, all clustering medians for each group will be used to represent the results for each group, i.e., the “micro-state.” Second, the time-series characteristics of the dFC microstates will be analyzed. The specific indicators include the average residence time of the microstate, conversion time, and stability.

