### fMRI outcome measures

We will use a Siemens’ 3.0 T superconducting magnetic resonance scanner and a 12-channel head coil for magnetic resonance scanning. All subjects will be scanned with the same parameters, and the same operator will be responsible for routine operations. An operator instruction manual will be produced to standardize the operation process and communication with the subjects. The various factors that can impact the magnetic resonance scanning (MRS) process will be strictly regulated. That is, the scanning time will be unified and the interference of the environment, equipment, technicians, and psychology on the subjects’ brain function imaging data will be limited, improving data reliability. The scanning parameters will be as follows: repetition time (TR): 2,000 ms, echo time (TE): 30 ms, field of view (FOV): 240 × 240 mm^2^, slice thickness (ST): 4 mm, number of slices (NOS): 40, matrix: 64 × 64, flip angle (FA): 90°.

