## Discussion

We hypothesized that the brain network mechanism of acupuncture serves as the multi-dimensional regulator of the key “DMN” brain network in CSU. To test this hypothesis, we will employ BOLD fMRI as the primary research method, as well as rsFC with strong spatial characterization, dFC with high sensitivity to time-varying characteristics, and microstate extraction as the main analysis methods. In this way, we aim to explore the pathological features of brain networks in patients with CSU in three dimensions: time, space, and microstates.

Microstate extraction technology will be used to identify subtle changes in the deep layers of the dynamic brain network. The “microstate” is a transient stable state found in many dFC studies (42). Specifically, the brain rapidly evolves into another state after maintaining a particular state for 80–120 ms; different states reappear over time. This analysis method has high sensitivity and specificity and can capture hidden dynamic changes based on dFC analysis.

In addition to studying the brain network, we will evaluate changes in the microbiota. Specific relationships between gut microbiota and CSU have been proven. Similar to the intestine, many skin microbiota are related to pruritus diseases (43). However, the direct relationship between skin microbiota and CSU remains unclear. Therefore, in this study, we evaluated the gut and skin microbiota to explain the pathological characteristics of CSU from a microbiota perspective.

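### Dynamic connectivity states are clustered subject by subject with no stated common reference, so comparability of state-specific dwell times is not secured; and the 80–120 ms duration given for them is beyond what the scan can resolve

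*Protocol article*

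**What the plan says.** The Protocol article, under Brain micro-states extraction technology, sets out these steps. Sliding-window connectivity vectors are formed for all participants. Vectors with high variability (above 1 SD) become the clustering samples, and the average cluster diameter decides one number of clusters. The states then come from "running the standard k-means algorithm with the optimal clustering number on each subject", applied to that subject's own vectors. Next, "all clustering medians for each group will be used to represent the results for each group", and these medians are named the micro-state. Residence time, conversion time and stability are analysed afterwards.

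The time scale is fixed in two other places. Under fMRI outcome measures the scan has "repetition time (TR): 2,000 ms". Under Dynamic functional connection analysis the plan uses "a window length of 30TR (60 s) and a sliding step size of 1TR will be applied to generate 200-time windows".

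The Discussion says that the microstate "is a transient stable state found in many dFC studies", and continues that "the brain rapidly evolves into another state after maintaining a particular state for 80–120 ms".

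**The concern.** There are two separate problems.

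**State definition.** The number of clusters is the only quantity that the text visibly carries from the all-participant step to the subject-level step. k-means numbers its clusters arbitrarily, and its centroids depend on the data it is given. If each subject is clustered alone, a given state in one subject need not be the same connectivity pattern as the state with that number in another subject, in the other arm, in the healthy controls, or in the same patient after treatment. A residence time for that state then has no fixed meaning across the comparisons of interest. Change in a patient's own centroids and change in time spent in a state also become hard to separate.

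**Time scale.** The states are extracted from windowed connectivity, but are described as lasting about a tenth of a second. A reader would take the residence times as evidence on sub-second dynamics, which this acquisition cannot supply.

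The Discussion lists microstate extraction among the main analysis methods, so part of the mechanistic conclusion would rest on these indices.

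**Working it through.** **Inputs.** Repetition time 2,000 ms (fMRI outcome measures). Window 30 TR, step 1 TR, 200 windows (Dynamic functional connection analysis). Ten initial volumes discarded, "removing the first 10 time points" (Neuroimaging data preprocessing). State duration 80–120 ms (Discussion).

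**1. The plan's own figure.** 30 × 2.0 s = 60 s. The stated window length is reproduced.

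**2. Scan length implied.** Retained volumes = (200 − 1) × 1 + 30 = 229, or 229 × 2 s = 458 s. With the 10 discarded volumes this is 239. Non-overlapping windows: 229 / 30 = 7.6. The 229 is inferred from the window count; the article does not state it.

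**3. Sampling against the stated duration.**
- TR / duration: 2,000 / 120 = 16.7; 2,000 / 80 = 25.
- Window / duration: 60 / 0.12 = 500; 60 / 0.08 = 750.
- Shortest recordable residence time: one step, 1 × 2 s = 2 s, which is again 16.7 to 25 times the stated duration.

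One window therefore averages over 500 to 750 states of the described length.

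**4. What passes between the clustering steps.**

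| Step in the text | Data used | What is passed on |
|---|---|---|
| Choose the number of clusters | high-variability vectors, all participants | the number |
| Run k-means | each subject's vectors | that subject's clusters |
| Summarise | clusters within a group | group medians, called the micro-state |
| Temporal indices | not stated which centroids | residence time, conversion time, stability |

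No row states a set of centroids shared by everyone, or a rule that matches one subject's clusters to another's.

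**5. Illustration of dependence on the clustering scheme.** Simulated noise containing no states was analysed: 50 subjects, 5 regions, 229 volumes, 30-TR windows, 200 windows. The number of clusters (3, 4, 5) and the noise model (white, or first-order autoregressive with coefficient 0.4) are assumptions.

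| Noise | Clusters | Mean dwell, by subject (s) | Mean dwell, pooled (s) | Ratio |
|---|---|---|---|---|
| white | 3 | 61.4 | 22.2 | 2.8 |
| white | 4 | 52.7 | 18.8 | 2.8 |
| white | 5 | 48.5 | 18.9 | 2.6 |
| AR 0.4 | 3 | 71.4 | 28.6 | 2.5 |
| AR 0.4 | 4 | 53.2 | 20.1 | 2.6 |
| AR 0.4 | 5 | 49.0 | 19.7 | 2.5 |

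Dwell times of tens of seconds arise with no states present, and they change about 2.5- to 2.8-fold with the clustering scheme. This compares two schemes, not two arms under one scheme, so it is not evidence of a false treatment difference.

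**The case against.** The strongest reply on state definition is that the wording allows another reading. The pooled step may produce a solution that the subject-level run starts from, and a condensed article may leave initialisation and matching to the full protocol. That stands in part. A reader might infer that the results are certainly not comparable, and the text does not establish that. What remains is that the article does more than stay silent: it positively specifies subject-level runs and group-level medians as the definition of the state.

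A second reply is that patients are randomised and the analysts are blinded. If every subject is processed identically without regard to arm, arbitrary labels are exchangeable between arms when acupuncture has no effect. This also stands. A reader might infer that the scheme manufactures a treatment difference, but between randomised arms it mainly adds noise and costs power. Distortion would need dwell times computed against each group's own centroids, which the article neither states nor rules out. The protection from randomisation does not extend to comparing patients with healthy controls or one session with another.

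Third, mean dwell over all states and the number of transitions do not depend on label order. That is correct, but both still depend on each subject's own centroids.

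On time scale, the Discussion claims only that the method can pick up hidden dynamic changes. A reader might infer an explicit claim to measure sub-second states, and no such sentence exists. The duration is nevertheless attached to the very object being extracted, so the contradiction with the acquisition settings remains.

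**Conclusion.** The point holds in two parts of different certainty.

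The time-scale contradiction is firm and rests only on stated figures. States of 80–120 ms cannot be resolved with a TR 17 to 25 times as long and a window 500 to 750 times as long. The indices describe connectivity averaged over a minute, recorded in 2 s steps.

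On clustering, the conclusion is that comparability of state-specific indices across subjects, arms, controls and sessions is not secured by the method as written. It rests on reading the number of clusters as the only item carried forward, which is the plain sense of the text but not the only possible one. Its effect on the arm comparison cannot be quantified from the article; loss of precision is the likelier consequence, with distortion if group-specific centroids are used. The issue should be corrected, because a better-defined method is available at little cost. It does not touch the primary outcome, UAS7.

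**What to change.** 1. Fit k-means once on windows pooled over all participants and both sessions, blind to group, initialised from the high-variability vectors that the plan already selects. If all scans are usable this is 50 × 2 + 25 = 125 sessions, or 125 × 200 = 25,000 windows.
2. Assign every window of every subject to these common centroids, and derive residence time, transitions and stability per subject and session. Use group medians for display only.
3. Remove the 80–120 ms description from the Discussion and call the output window-level dFC states.
4. Report dwell times in windows or seconds, with the 60 s window and 2 s step stated beside them.

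The cost is some rewording and recoding, with no new data, and a less ambitious claim about fast dynamics. If the pooled solution is in fact already carried forward to each subject, one sentence saying so would settle the clustering part.
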